# The coMforT study of a trauma-informed mindfulness intervention for women who have experienced domestic violence and abuse: a protocol for an intervention refinement and individually randomized parallel feasibility trial

**DOI:** 10.1186/s40814-019-0527-1

**Published:** 2020-02-28

**Keywords:** Domestic violence and abuse (DVA), Trauma, Post-traumatic stress disorder (PTSD), Mindfulness, Mindfulness-based cognitive therapy (MBCT), Intervention development, Feasibility trial

## Abstract

**Background:**

Domestic violence and abuse (DVA) is common and destructive to health. Post-traumatic stress disorder (PTSD) is a major mental health consequence of DVA. People who have experienced DVA have specific needs, arising from the repeated and complex nature of the trauma. The National Institute for Health and Care Excellence recommends more research on the effectiveness of psychological interventions for people who have experienced DVA. There is growing evidence that mindfulness-based interventions may help trauma symptoms.

**Methods:**

Intervention refinement and randomized controlled feasibility trial. A prototype trauma-informed mindfulness-based cognitive therapy (TI-MBCT) intervention will be co-produced following qualitative interviews and consensus exercise with stakeholders. Participants in the feasibility trial will be recruited from DVA agencies in two geographical regions and randomized to receive either TI-MBCT or usual care (self-referral to the Improving Access to Psychological Therapies (IAPT) service). TI-MBCT will be delivered as a group-based eight-week program. It will not be possible to blind the participants or the assessors to the study allocation. The following factors will inform the feasibility of progressing to a fully powered trial: recruitment, retention, intervention fidelity, and the acceptability of the intervention and trial design to participants. We will also test the feasibility of measuring the following participant outcomes before and 6 months post-randomization: PTSD, dissociative symptoms, depression, anxiety, DVA re-victimization, self-compassion, and mother-reported child health. Process evaluation and economic analysis will be embedded within the feasibility trial.

**Discussion:**

This study will lead to the development of a TI-MBCT intervention for DVA survivors with PTSD and inform the feasibility and design of a fully powered randomized controlled trial (RCT). The full trial will aim to determine the effectiveness and cost-effectiveness of a TI-MBCT intervention in improving the clinically important symptoms of PTSD in DVA survivors.

**Trial registration:**

ISRCTN, ISRCTN64458065, Registered 11 January 2019.

## Background

### Mental health consequences of domestic violence and abuse

Domestic violence and abuse (DVA) is a major public health and clinical problem which is experienced by 1 in 4 women and 1 in 7 men in England and Wales [1]. Although DVA is experienced by both women and men, the impact on health is greater among women [2]. Between 6% and 17% of women attending primary care report having been abused by a partner in the past year [3]. The single biggest cost associated with DVA is to the NHS: £1.7 billion per year, with the major cost borne by acute trusts and primary care. Mental health service costs are estimated to be an additional £176 million [4].

A major mental health consequence of DVA experienced by women is post-traumatic stress disorder (PTSD), with a 7.3 odds ratio for the experience of intimate partner violence in women with PTSD [5]. Another study found a two-fold increase in the prevalence of PTSD among women with higher levels of exposure to DVA [6]. A psychiatric morbidity survey in England found that 12.6% of women aged 16 to 24 screened positive for PTSD [7]. Symptoms of PTSD include reliving the traumatic experience, hypervigilance, avoidance, and cognitive distortions often related to beliefs about safety, power, and self-worth that impair the ability to break the cycle of abuse [8, 9]. Although research findings suggest a spontaneous recovery of PTSD in some people who have experienced DVA, a significant number (46.8%) of women exhibit chronic PTSD [10].

In contrast to single-event trauma, DVA occurs repeatedly and often increases in severity over time [11]. Women who have experienced DVA represent a distinct patient group due to the complexity of their trauma and its specific impact on affect regulation, changes in consciousness, sense of self, relationships, and belief systems [12]. Survivors of DVA often have numerous and cumulative psychosocial stressors, including poverty, lack of social support, parenting stress, and ongoing contact with the perpetrator through child contact [9, 13]. For these women, accessing standard trauma-focused treatments can be practically difficult and emotionally problematic [14–16]. There is also the need to address safety and the risk of re-traumatization if there is ongoing contact with the perpetrator [17]. The stigma associated with mental health symptoms also leads to decreased use of mental health services; women who have experienced DVA may fear that a mental health diagnosis will result in their children being removed from their care [13, 18].

### Impact on children

Children in families affected by DVA are at higher risk of developmental and behavioral problems, compromising their lifelong wellbeing and functioning [19]. Children whose mothers have experienced DVA and have PTSD and depression are at higher risk of behavior problems [20].

### Evidence-based interventions for PTSD

The National Institute for Health and Care Excellence (NICE) guidance on PTSD advocates individual trauma-focused cognitive behavior therapy (TF-CBT) and eye movement desensitization and reprocessing (EMDR) as evidence-based treatment options [21]. A Cochrane review [22] showed that both therapies performed better than usual care for reducing symptoms of PTSD. Both therapies use exposure work, requiring participants to directly confront their traumatic stories. In addition, many of the study populations identified in the review had experienced single event traumas. A significant proportion of PTSD sufferers either do not seek help, drop out of or decline these treatments, or continue to meet diagnostic criteria for PTSD after trauma-focused interventions [23]. The NICE guidance recommends more research on the effectiveness of psychological interventions modified for DVA [24].

In contrast to trauma-focused approaches, mindfulness-based interventions do not include exposure work and therefore could be more acceptable to survivors of DVA. Mindfulness-based interventions have recently received increased attention for helping patients who have experienced trauma [25, 26]. A recent systematic review [25] which included four studies with people who have experienced childhood abuse and DVA found some evidence that mindfulness-oriented interventions may decrease PTSD symptoms, although most studies were underpowered and had methodological weaknesses. The review identified the need for further modification of mindfulness interventions for PTSD and further adequately powered randomized controlled trials (RCTs) of the modified interventions.

### Pre-protocol development of a mindfulness intervention for DVA trauma

This study is built on pre-protocol development work carried out in 2014–2015: (i) a synthesis of prior literature on mindfulness-oriented interventions for DVA and PTSD, (ii) consultations with a group of DVA survivors on potential adaptations to standard mindfulness treatment, (iii) consultation with mental health professionals on the rationale behind mindfulness approaches for PTSD in the DVA population, (iv) consultation with DVA advocates on the safety of mindfulness approaches for women who have experienced DVA, and the feasibility of recruitment through third sector DVA agencies. Informed by this work, a mindfulness teacher with expertise and experience in trauma developed a trauma-informed intervention by modifying the standard manual for preventing depression relapse (mindfulness-based cognitive therapy (MBCT)) ([name]: How can an adapted MBCT course meet the specific vulnerabilities of women survivors of domestic violence and abuse? Unpublished thesis: Bangor University; 2015). This adaptation process was overseen by a mindfulness-based supervisor with expertise in trauma. We call this modification a trauma-informed mindfulness-based cognitive therapy (TI-MBCT) prototype 1. This prototype intervention was pre-piloted with a group of women who had experienced DVA and their feedback was obtained through a group interview. The feedback from the pre-pilot testing suggested that the prototype TI-MBCT program may be acceptable to a DVA population and might be effective but required robust evaluation with a randomized controlled design. Our pre-protocol development work identified several areas of uncertainty about the future trial associated with:
Choice of the control intervention. In a definitive trial, the control intervention will be an evidence-based manualized psychological intervention for PTSD currently available within NHS Improving Access to Psychological Therapies (IAPT) services. Our primary intention was to use trauma-informed cognitive behavioral therapy (TI-CBT). However, consultations with service user and professional stakeholders revealed that in DVA agencies women with mental health problems are signposted to their GPs and IAPT services. The latter offers varied treatments (e.g., trauma counseling, TF-CBT, EMDR) depending on an individual’s symptoms and needs and practitioners’ availability.Recruitment of DVA survivors with PTSD through third sector DVA serviceThe randomization of DVA survivors with PTSDRetention of DVA survivors with PTSD in the trialUptake, retention, and acceptability of the modified MBCT intervention to DVA survivors with PTSDData collection methods.

The coMforT (Mindfulness for Trauma) study addresses these areas of uncertainty through further intervention development work with stakeholders followed by feasibility testing of the refined intervention.

## Methods/design

### Study aim/objectives

The coMforT study aims to (i) produce a TI-MBCT program that is acceptable to DVA survivors with PTSD and feasible to deliver and (ii) establish the feasibility of a definitive trial of a TI-MBCT intervention vs control intervention for this population.

The objectives of the intervention development work are to
Elicit service users’ and professional stakeholders’ suggestions for recruitment and retention of DVA survivors with PTSD and their uptake and engagement with the prototype TI-MBCTElicit service users’ and professional stakeholders’ suggestions for additional refinements of the prototype TI-MBCT that will increase uptake and engagement with the intervention.Produce TI-MBCT manual for feasibility testing.

The objectives of the subsequent feasibility trial are to
Determine which psychological intervention currently offered within the NHS IAPT service can be used as control intervention in a definitive trial, and explore the practicality of referring study participants to this control interventionAssess the feasibility of recruiting participants through third sector organizations providing health and social care to DVA victims and survivorsEvaluate the acceptability of randomization to participantsDetermine if it is possible to retain DVA survivors with PTSD to follow-upRefine the orientation process for the TI-MBCT interventionExamine if it is possible to enroll and retain DVA survivors with PTSD in TI-MBCT groupsEvaluate the acceptability of the TI-MBCT intervention to DVA survivors with PTSDDetermine the practicalities of delivering TI-MBCT in the community settingProduce TI-MBCT manual for the full-size trialExamine the acceptability and completeness of the data collection methods for a definitive trialEstimate variance and distribution of quantitative outcomes in the feasibility trial data to inform the design and sample size calculation in the future definitive trial.

A traffic light system will be used to review progression criteria to a full trial, whereby “green” indicates that it is feasible to conduct a definitive trial with the current trial design and procedures, “amber” indicates that improvements are required before conducting a definitive trial, and ‘red’ indicates that it is not feasible to progress to a definitive trial (see Table 1). The independent study steering group will be consulted about whether progressing to a definitive trial is justified.

**Table 1 Tab1:** Criteria for progression from feasibility trial to full-size trial

Progression criteria	Measurement	Green	Amber	Red
Recruitment	Number of participants recruited over 6 months	24	12–23	< 12
Recruitment	Qualitative process evaluation	Most participants find the recruitment procedures acceptable or only minor amendments needed.	Participants’ views on acceptability conflicting or larger changes needed.	Most participants find unacceptable or changes needed unfeasible.
Randomization	Qualitative process evaluation	Most participants understand the randomization process and find it acceptable.	Participants’ understanding and views on acceptability conflicting.	Most participants do not understand process or find it unacceptable
Follow-up (total and by trial arms)	Proportion of enrolled participants providing primary outcome data at 6 months post-randomization	> 50%	31–50%	≤ 30%
Follow-up (total and by trial arms)	Qualitative process evaluation	Most participants find the follow up process acceptable or only minor amendments needed.	Participants’ views on acceptability conflicting or larger changes needed.	Most participants find processes unacceptable or changes needed unfeasible.
Uptake of TI-MBCT	Proportion of participants who took up the mindfulness group out of those randomized in the intervention arm [27, 28]	> 70%	50–69%	< 50%
Retention in TI-MBCT group	Proportion of participants in the intervention arm who received at least four sessions [29, 30]	≥ 60%	40–59%	< 40%
TI-MBCT acceptability	Qualitative process evaluation	Most participants find the mindfulness group acceptable or only minor amendments needed.	Views on acceptability conflicting or larger changes needed.	Most participants find unacceptable or changes needed unfeasible.
Data collection methods	Qualitative process evaluation	Most participants find the data collection procedures acceptable or only minor amendments needed.	Views on acceptability conflicting or larger changes needed.	Most participants find unacceptable or changes needed unfeasible.

Note: *TI-MBCT* trauma-informed mindfulness-based cognitive therapy

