**Fig. 1. Fig1:**
[figure not shown]
Flow diagram of randomized feasibility trial of two consecutive TI-MBCT groups vs NHS IAPT service https://www.spirit-statement.org/. TI-MBCT trauma-informed mindfulness-based cognitive therapy. NHS National Health Service. IAPT Improving Access to Psychological Therapies. PTSD Post-traumatic stress disorder

From the pool of service users in third sector DVA agencies, women with PTSD will be recruited and randomized (2:1—intervention:control). The participants in the intervention arm will take part in a group-based TI-MBCT course and participants in the control arm will be asked to self-refer through the IAPT service. Participants will be followed up at 6 months post-randomization. In the intervention arm, we will run two consecutive TI-MBCT groups. The first group will receive the TI-MBCT prototype 2 produced through the intervention development phase. At the end of the first group, we will interview the participants to inform further intervention refinement and produce the TI-MBCT prototype 3 for the second intervention group. After the second group, we will invite participants to take part in further qualitative interviews, as part of a process evaluation. Results of the feasibility trial and process evaluation will inform a decision on progression to a full-size trial. If we find that it is feasible and acceptable to progress (see Table 1), we will produce a final version of the TI-MBCT manual for the full-size trial.

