#### Feasibility trial

The required sample size is based on the precision for estimating the proportion (30%) of eligible participants consenting to participate in the study. If 120 eligible women are screened, then a true recruitment rate of 30% (= 36 recruits) will be estimated as between 21.8 and 38.2%, with 95% probability. This estimate is based on a previous trial that successfully recruited women from one of the collaborating DVA services [27, 52]. Based on previous trials of psychological interventions for women who have experienced DVA [27, 28] up to 33% of the consented and randomized participants are expected to drop out before the start of the mindfulness group/control intervention. Therefore, 54 will be randomized in order to be left with 36 who will be allocated to the intervention or control arm. We will compare the rate of drop out before starting mindfulness/control interventions between the two arms of the trial.

Retention will be optimized using established methods for trials involving women who have experienced DVA, [53–55] further modified through previous research in the UK context [56, 51], which resulted in 70–81% retention rates. The methods include maintaining a safe contact list, reimbursement for travel, childcare and £20 shopping voucher for each treatment session attended.

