#### Feasibility trial

Data regarding feasibility will be obtained from study logs of recruitment and follow-up, therapists’ records about intervention uptake/sessions attended, retention and dose received, and interviews with participants about the acceptability of the intervention and trial design. Clinical data will be collected at face-to-face meetings with the researcher using the standardized validated questionnaires listed above. Economic data will be collated from the study logs detailing the cost of intervention delivery. Self-reported economic measures will be collected from participants 6 months post-randomization using paper-based, self-completed, and interviewer-assisted questionnaires.

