### Withdrawal criteria

Participants may withdraw because they no longer wish to attend the intervention or control therapy or assessment meetings or because a change in their health status or personal circumstances warrants their withdrawal. Researchers will attempt to contact participants up to three times using different modalities (e.g., text, email, and phone), before deeming them to be lost to follow-up. Data obtained up to the point of withdrawal will be anonymized and retained for analysis. Participants who have withdrawn or dropped out of the study will be contacted once by telephone and asked if they would agree to answer some questions to explore the reasons for their non-participation. This will be explained in the participant information sheet and consent form.

It is hoped that participants withdrawing from the intervention or control arm would remain willing to participate in follow-up measurements at 6 months; all participants withdrawing from the intervention/control phase will be approached once at the 6-month point, but contact will not be pursued if participants either (i) indicate that they do not wish to complete the follow-up stage or (ii) do not respond.

In the circumstance that a participant wishes to withdraw from the trial and therapy completely, they will no longer receive contact from the mindfulness teacher (if in the intervention arm), or from the IAPT therapist (if in the control arm) and will not be contacted about follow-up research appointments.

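### The Table 1 rows on acceptability of recruitment and randomization hear only from women who have already agreed to both, so refusal of chance allocation could go unseen

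*Protocol article*

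**What the plan says.** All references are to the protocol article. Table 1 (Study aim/objectives) sets traffic-light criteria for progression. Recruitment has a count over 6 months (green 24, amber 12–23, red below 12) and a qualitative row. Randomization has a qualitative row only, green when "Most participants understand the randomization process and find it acceptable".

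Data collection methods (Feasibility trial) names the source of the acceptability evidence: "interviews with participants about the acceptability of the intervention and trial design". Under Recruitment and consent (Feasibility trial), randomization follows informed consent and baseline data collection.

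Sample size (Feasibility trial) rests on the precision of the "proportion (30%) of eligible participants consenting to participate in the study". Table 4 defines a recruitment rate with eligible women as the denominator, but Table 1 attaches no threshold to it.

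On timing, the text with Fig. 1 states: "At the end of the first group, we will interview the participants". Under Withdrawal criteria, women who withdraw or drop out are to be "contacted once by telephone and asked if they would agree to answer some questions to explore the reasons for their non-participation".

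**The concern.** Whether this population will accept randomization is one of the uncertainties listed in the Background, an objective of the feasibility trial, and a theme of the Discussion. The row meant to settle it selects on its own outcome: a woman who does not want to be allocated by chance, or would accept only one of the two arms, declines and never becomes a participant whose view is sought.

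The filter may act even earlier. Initial screening (Table 2) asks about readiness to start either the mindfulness group or an NHS talking therapy, and support workers refer on only women willing to be contacted.

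Table 1 defines green as feasible with the current design and procedures. That depends on women who refuse as well as on those who agree. The steering group could be advised that randomization is acceptable when the evidence comes only from women who had accepted it.

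**Working it through.** **Inputs.** Consent rate 30%, 120 eligible women, 33% loss before treatment starts, 54 randomized (Sample size); 2:1 allocation (Study design); Table 1 bands.

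**1. The plan's own figures.** The plan says "a true recruitment rate of 30% (= 36 recruits) will be estimated as between 21.8 and 38.2%, with 95% probability". The Wald interval is 0.30 ± 1.96 × √(0.30 × 0.70 / 120) = 0.30 ± 0.082, or 21.8% to 38.2%, which agrees. The number randomized is 36 / (1 − 0.33) = 53.7, rounded up to 54, which also agrees.

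**2. Women outside the two rows.** 120 × 0.30 = 36 consent and 120 − 36 = 84 (70%) do not. If 54 are randomized at the same rate, 54 / 0.30 = 180 eligible women are needed and 180 − 54 = 126 do not join. The 70% is implied by the 30%, not stated, and covers every reason for not joining.

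**3. Can the recruitment count stand in?** Green is 24 recruits. That is reached from 80 eligible women at 30% (80 × 0.30 = 24) or from 240 at 10% (240 × 0.10 = 24). The count is the same at very different refusal rates, and a low count would not reveal the cause.

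**4. Can another row stand in for randomization?** No. Every other row with a numerical measure apart from recruitment (follow-up, uptake, retention) starts from enrolled or randomized women.

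**5. Women who leave after randomization.** The plan expects that "up to 33% of the consented and randomized participants are expected to drop out before the start of the mindfulness group/control intervention". At 2:1, 54 × 2/3 = 36 are in the intervention arm and about 12 of them leave before the group starts, so expected uptake is 24/36 = 66.7%. That lies in the amber band (50–69%). With uptake binomial(36, 2/3), green needs at least 26 (26/36 = 72.2%; 25/36 = 69.4% falls short). The probabilities are about 0.30 green, 0.68 amber (18–25) and 0.01 red (under 18). Leavers are therefore visible in Table 1.

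**6. Timing of the first interviews.** Recruitment runs in 2-month windows before each group and the course lasts eight weeks. The end of group 1 is thus roughly 2 to 4 months after randomization, before the 6-month assessment that the follow-up acceptability row judges.

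**The case against.** The objective is to evaluate acceptability of randomization to participants, and the row measures that. The row is not automatically green: it also tests understanding, women allocated to IAPT can object once they know their arm, the analysis looks at the arms separately and seeks disconfirming cases, and conflicting views are enough for amber. The rate over eligible women will be reported with a confidence interval, and the steering group is consulted. The article does not list the fields of the recruitment log, so reasons for declining may already be recorded under the full protocol.

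Much of this stands. It rules out saying that the row is green by construction, or that the study will certainly hold no information on refusal. It does not remove the point. Even if the log records reasons, Table 1 as written makes no use of them, and the reported rate carries no threshold and no cause.

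A reader might also infer that the third expected to leave before treatment are equally invisible. The documents do not support that. These women are randomized participants, they receive a call about their reasons, and they count in the uptake and retention rows. Only a minor point remains: the call is single and optional, and it is not expressly tied to the TI-MBCT acceptability row.

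On timing, nothing says the group 1 interviews are the only source for the follow-up row. Later interviews are planned without a stated date, and the researcher meets women at 6 months.

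**Conclusion.** The point holds for the qualitative recruitment row and, above all, for the randomization row. Both are scored on women who have consented, and at the plan's own rate about 84 of 120 eligible women contribute no acceptability evidence to them. No other Table 1 row shows whether refusal of chance allocation is a barrier.

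The size rests on the planned 30% consent rate. How many of the 84 would decline because of randomization is unknown, and the documents give no basis for a figure, so none is offered for acceptability among all eligible women. This is a weakness in a stated decision rule that should be put right at little cost. It is not an arithmetical error, and it does not affect the sample size.

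**What to change.** 1. Add an optional main reason for declining to the existing recruitment log, completed by the support worker or researcher. Include not wanting allocation by chance, wanting mindfulness only, and not wanting IAPT. If the log already has such a field, only step 2 is needed for these two rows.
2. Reword the recruitment and randomization rows of Table 1 so that these reasons and the recruitment rate over eligible women are considered beside the participant interviews. State that the randomization row is not green if refusal of randomization is a common recorded reason, and fix in advance what counts as common.
3. Minor additions: state that reasons from the existing withdrawal call inform the TI-MBCT acceptability row, and ask about follow-up acceptability at the 6-month meeting.

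The cost is one log field, a few questions at an existing visit, and Table 1 wording. Some women will give no reason, so the evidence will be partial, and the rows may look less favourable.
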